### Eligibility of workplaces for entering the study

#### Workplace (cluster) inclusion criteria

•Workplaces in industry that was primarily office-based and sedentary in nature, such as government administration departments, publishing industry, property development and finance industry.

•Workplaces that were able to recruit at least 30 female employees engaged in desk-based jobs (sitting for at least 50% of working hours).

•Agreement to permit up to 10 hours of paid work time during the course of the study (12 months) for the recruited employees to participate in pre-post data collection and intervention activities.

### Eligibility for within-cluster recruitment

Within-cluster inclusion criteria were:

•Being female

•Age 25–49 years of age

•Being in a sedentary job (at least 50% of work hours seated)

Within-cluster exclusion criteria were:

•Being pregnant or lactating

•Diagnosed osteoporosis

•Diagnosed kidney problems

•Participation in another health program that addresses diet and/or physical activity

### Recruitment

#### Cluster (Workplace) recruitment

Clusters were sampled from database of workplaces who were recipients of 2003 Singapore Health Award. These workplaces would have demonstrated commitment to promoting employee health to receive this national award, hence the characterisation of this trial as assessing efficacy rather than effectiveness.

Generic invitation letters were mailed to 97 workplaces to invite them to participate in this study. The letter stated the objectives of the study but did not detail the nature of interventions. It stated that a briefing would be conducted to provide them with the details. A faxed reply from the workplace was requested to confirm participation by a stipulated date.

Thirty-seven faxed replies were received by the stipulated deadline. The workplaces’ names were arranged in a data sheet according to the date and time of receipt. Eligibility was on a first-come-first served basis. When sufficient clusters (workplaces) had been recruited, the subsequent workplaces who responded were placed on a reserve list also in order of the date and time of receipt. The workplaces (clusters) that have been recruited were labelled WP1 to WP16 according the date and time of the fax.

#### Cluster randomisation process

When the cluster recruitment process was completed, a statistician generated a set of random numbers for the list of workplaces recruited. The statistician had no access to the faxed replies and was blinded to the identities of the workplaces. The random numbers were generated for the labels WP1 to WP16. When the random number had been assigned to the workplace, the names of the workplaces were re-arranged according to the random numbers assigned in ascending order (smallest number first and biggest number last). The first eight workplaces in this new arrangement were assigned to the intervention group and the subsequent eight workplaces were assigned to the control group. Workplaces recruited were in government administration, property development, finance, publishing and energy provision industries.

Following randomisation, workplace coordinators from the two groups were invited to two different briefings, depending on assignment to the intervention or control group. The briefings provided intervention and control group-specific information to respective workplace coordinators. The briefings also detailed the commitment required of the workplaces, the (within-workplace) recruitment process and the nature of assessments (data collection procedures). The workplaces in both groups were blinded to the type of intervention that the other groups were to receive. It was considered highly unlikely that unblinding would occur, as the workplaces were not geographically close. Figure 
1 summarises the recruitment and randomisation process.

**Figure 1 F1:**
[figure not shown]
Recruitment and randomisation flow chart.

#### Within cluster recruitment (individuals)

When the workplace (cluster) allocation process was completed, workplace coordinators from both groups were contacted to commence the within-cluster recruitment process. The coordinator was provided with resources (such as posters, e-mailers) to publicise the recruitment. Employees who expressed interest were screened for eligibility before being recruited into the study. Over-recruitment by 30 percent to account for attrition was planned. Workplaces that recruited more than 30 respondents would create a waiting list in the event of withdrawal before commencement. Workplaces with less than 30 respondents would include all eligible respondents in the study.

### Ethics approval

The study was carried out as part of the Health Promotion Board Osteoporosis Prevention Programme initiative. The study was reviewed and approved by the Health Promotion Board (Singapore) Research and Ethics Committee before commencement.

### Consent

All recruited employees were provided with a consent form, accompanied by print information about the study. The content of the information sheet and their right to withdraw were explained to the recruits during their individual appointment with the investigator. Signed consent forms had to be returned to the investigator before the employees could formally enrol. The information sheet stated that the right of any subject to cease participation without giving reasons would be respected.

### Ethical considerations for the control group

Educational resource distribution was a strategy that was already in place for promoting bone health awareness in many Singaporean workplaces. Resources on osteoporosis prevention were widely distributed through various platforms such as community events, workplaces and health facilities. It would not be appropriate for workplaces in the control arm to receive less than an existing intervention, hence the standard care control.

The purpose of the study was to investigate if a more targeted and structured intervention with organisational support is more efficacious than existing practice. It was important to maintain the existing practices/strategy for the control group for the comparison to be purposeful, and to determine the extent to which current practice can be improved upon. These were the key ethical considerations for the study design.

### Data collection

Data for the two outcome measures, calcium intake and physical activity, were collected at three time points for both study arms. The mediators in this study, self-efficacy scores for calcium intake and physical activity, were also collected at the same time points. Demographic and lifestyle information were collected at baseline.

The three data collection points were:

•Baseline: four weeks before the intervention

•Four weeks after the intervention workshops (for the intervention group) were completed

•Six months after the first post-intervention data collection was completed

Data collection for both the intervention and control arms took place during similar periods at every time point. Figure 
2 provides an overview of the timeline for data collection.

**Figure 2 F2:**
[figure not shown]
Data collection and intervention timeline.

### Outcomes measures

The outcome measures in this study are

•Daily dietary calcium intake (milligrams per day)

•Total moderate to vigorous load-bearing leisure time physical activity duration per week (minutes)

### Mediators

The hypothesised intervention-specific mediators of improvement in outcomes in this study are (see also Figure 
3):

•Self-efficacy scores for calcium intake

•Self efficacy scores for exercise

**Figure 3 F3:**
[figure not shown]
Logic model for the intervention group.

### Dietary calcium intake data collection method

Calcium intake was measured using a three-day diet record. This method involved each participant keeping a detailed written record of the foods and beverages consumed over three days. Three day recording was selected as recording periods of more than three or four days were reported to be unreliable due to respondent fatigue
[35]. Specific emphasis was put on the correct description of portion sizes so that an accurate estimate of calcium content could be derived.

An appointment was scheduled to meet each participant individually to provide specific instructions for completion of the three-day diet record. The three days would include two representative weekdays and one representative weekend day. Completed dietary records were collected and sent to a qualified nutritionist for analysis to establish the calcium content. The nutritionist was blinded to the treatment arms and the identities of the workplaces and participants.

### Physical activity duration data collection methods

Physical activity was measured using the EPIC Norfolk Physical Activity Questionnaire 2 (EPAQ-2). The EPAQ-2 was designed to measure the different sub-dimensions of physical activity in the Norfolk cohort of the European Prospective Investigation into Cancer (EPIC-Norfolk) in 1999
[36]. It is a self-reported questionnaire on disaggregated physical activity enabling the data be re-aggregated to the dimension of physical activity of interest, for example load-bearing activity of relevance to osteoporosis prevention. The EPAQ-2 has been validated against four-day heart rate measurement and was concluded to have the validity and repeatability/reliability to be used in a large-scale epidemiological study
[36]. The questionnaire consists of three sections: activity at home, work and recreation. Permission was obtained from Wareham and Jakes to adapt and use the instrument for this study.

The content of the EPAQ-2 was assessed for cultural appropriateness by a panel that included experts from inside and outside the Health Promotion Board (Singapore). Minor modifications were made to the list of recreation activities. Activities that were not relevant to local context, such as “digging, shovelling or chopping wood” were removed, and replaced with common local activities not included in the version developed for use in Europe, such as Tai Chi. Seventeen women at a workplace (not involved in the study) assessed the ease of reading using the Flesch reading ease score. They also provided feedback on the ease of understanding and the ease of completing the modified EPAQ-2. Minor changes were made to the language of instructions on the questionnaires to further increase ease of understanding. Prompts were added in sections where extra information needed to be provided, for example duration of each session recreation activity, to facilitate thorough completion of the questionnaire.

A copy of the EPAQ-2 was sent to each participant through the workplace coordinator. The participants completed the questionnaire independently and submitted it to the investigator at each data collection point. The investigator checked that the EPAQ-2 was completed according to instructions.

### Self-efficacy data collection

Self-efficacy was measured using the osteoporosis self-efficacy scale developed and evaluated by Horan et al. in 1998
[37]. Written permission was sought from the authors to use the instrument.

The content of the questionnaire was assessed for appropriateness to local context by a panel that included experts internal and external to the Health Promotion Board (Singapore). It was also validated for internal consistency and test-retest repeatability through an evaluation process involving 17 women at a workplace (not involved in the study). The original content was found to be relevant to the local context and the questionnaire to have appropriate reliability for use in this study.

Each subject was sent a physical copy of the questionnaire through the workplace coordinator. The completed questionnaires were returned to the workplace coordinator who collated the submissions and dispatched them to the investigator.

### Socio-demographic information and other measures

Demographic and other health information was collected using questionnaires. At baseline, this included smoking and alcohol habits, family history of osteoporosis, indicators of socio-economic status (such as personal and household income, education level), religious preference (potentially relevant to diet and physical activity), marital status and number of children in the household.

### Intervention methodologies

Subjects from workplaces assigned to the intervention group received three intensive workshops targeting behaviour change. The intervention design had a strong focus on behavioural strategies and was participatory in nature. Bandura’s Self–Efficacy Model was used to guide the workshop design for the intervention group. Bandura’s model states that self-efficacy affects health behaviour and its determinants by influencing goals and aspirations. The stronger the perceived self-efficacy, the higher the goals people set for themselves and the firmer their commitment to them
[38]. Bandura also proposed that individuals with high efficacy view impediments as surmountable by improvement of self-management skills, that they persevere and stay the course in the face of difficulties
[38].

Guided by these principles, the workshop design focused on individual goal setting and on building skill sets to attain individual goals. The design avoided presentation style communication and focused on behavioural strategies such as participatory skill building through hands-on activities, goal setting exercises, peer support and problem solving discussions. Attention was placed on helping participants identify individual barriers and build their capacity to overcome them. The intervention also addressed diet and physical activity as different entities that required different behavioural strategies. Though guided by the same principles, the workshops for diet and physically activity were unique in the nature and design of their activities.

### Intervention strategy development for calcium intake

Our study reviewed the content of interventions that reported positive outcomes for dietary calcium intake. These studies described strong behavioural strategies using participatory activities such as food preparation and tasting, nutrition label reading exercises, group discussions with exchange of ideas
[14,15,39]. Their interventions also placed emphasis on using specific examples relevant to the participants' lifestyles and tastes
[14,15,40], as well incorporating local food sources into activities. Evidence also suggested that the provision of calcium intake feedback might be an effective tool to improve the behaviour
[39]. These elements were used to guide the development of intervention content in this study.

In addition, we planned to incorporate quantitative and qualitative dietary information collected at baseline to help tailor intervention strategies. The dietary records would be inspected to identify the common food sources of calcium amongst the study population, as well as their consumption patterns and volumes. This information would also be used to tailor strategies that would be relevant to individual participants.

Common barriers to consuming calcium rich foods, identified in previous research include the perception that these foods are higher in price, are mainly dairy products and are high in fat. Taste aversion, mainly to dairy, has also been highlighted as a barrier. These issues were addressed individually in different components of the workshop. Food tasting was a very effective strategy to expose subjects to a wide range of foods that can provide a substantial calcium boost. The ability to correctly read and interpret nutrition labels was identified as a necessary skill to facilitate selection of calcium rich foods. Practical sessions on reading of food labels were included in the intervention.

Subjects in both the intervention and control group received individual feedback on their average calcium intake based on the diet record they submitted. Although the subjects in the control group received similar information about their calcium consumption, the intervention group had the benefit of using this individualised information during the workshop to develop a strategy to attain their recommended daily allowance whilst the former did not. A logic model of the intervention can be found in Figure 
3.

### Intervention strategy development for physical activity

Local media campaigns and community based health promotion activities on osteoporosis prevention have had a stronger focus on diet compared to physical activity in the lead up to the time of the study. Limited local public education sources were dedicated to discussing the impact of physical activity on bone health and more importantly, the types of physical activity that can reduce the risk of osteoporosis.

Physical activity behaviour can have very different psychosocial mediators from dietary behaviour. In this study, physical activity was regarded as a unique behaviour that required a different set of intervention strategies to that for dietary calcium intake.

The types of physical activity that can affect bone mineral density, risk of osteoporosis and risk of fractures are described as load bearing and resistance training exercises
[41,42]. The intensity of activity is also critical. Evidence indicates that only moderate to vigorous level of load-bearing physical activity can affect bone density in important sites such as the hips, a vulnerable site for osteoporotic fractures
[43,44].

Studies about physical activity behaviour in the context of bone health are limited to adolescent populations and were carried out mainly in school settings. Strategies for adolescents cannot be used to guide the content development for this study. There are many studies on prescriptive exercise regimes but the interventions were aimed at studying bone density in response to exercise interventions, not physical activity uptake behaviour. The attrition rates for these studies are very high as behaviour modifications were not a focus.

In the absence of evidence in adult populations, this study evaluated the methodologies from studies that targeted general physical activity in community settings, including workplaces. It is important to note that whilst this study used workplaces as settings or delivery platforms, it did not have sufficient resources to implement changes to workplace environments and policies. This study aimed to improve individuals' self-efficacy to bring about behaviour change. Workplaces provided a platform to support change at the individual level through the provision of infrastructure for communication, peer support and common interest.

Evidence indicates behavioural strategies to be superior to cognitive strategies
[19,45]. Meta-analyses of physical activity interventions emphasise the importance of behavioural interventions, which include goal setting, self-monitoring, physical activity behaviour feedback, consequences, exercise prescription and cues
[19,45]. Our study adhered to these recommendations when designing intervention activities. In addition, emphasis was placed on providing opportunities to sample a variety of the targeted physical activities. These included take home activity samplers in many formats, including DVDs.

The first workshop discussed the relationship between load bearing and resistance training exercises on bone cell formation and bone modelling. This served to communicate the key message that specific types of exercise are needed to protect and promote bone health. The third workshop was focused entirely on helping participants identify their barriers to increasing their physical activity level and to help them overcome the barriers with individually tailored strategies.

The intervention for physical activity was facilitated by a physiotherapist and the investigator. The aims of the intervention were to encourage participants to problem solve and develop strategies to help them increase their moderate to vigorous intensity load-bearing physical activity by 60 minutes per week. Each participant would record their weekday and weekend routine to be shared within a group. In the design of the intervention, peer support was identified as an important mediator for behaviour change and hence the emphasis on group work. This allowed participants to identify common barriers to change, develop strategies together and support one another through problem solving on common issues. Workshop participants shared a common work environment and would be able to develop workplace based strategies based on shared experience. This facilitated discussion as participants shared many ideas that were based on common experience, such as workplace stair access for opportunistic physical activity, discussion of suitable walking routes around the workplaces and sharing of information about exercise facilities near the work premises.

Almost 50% of Singapore adults cited lack of time as a barrier to leisure time physical activity
[22]. Unique strategies were developed for this study to facilitate the attainment of the physical activity goal with minimal disruption to the participants’ routine. One important strategy was to introduce short bouts of exercise breaks (5–10 minutes) during television viewing time or work time, which many participants would regard as achievable and sustainable. Participants would devise different types of 5–10 minute exercise routines that required minimal room and could be carried out easily at home or at the workstation. Resources, such as an exercise CD and a 10-minute exercise poster with instructions and illustrations would be provided to each participant. The latter was developed specifically for this intervention.

### Control arm

Participants in control/standard care workplaces would receive a resource kit with general print resources on bone health and osteoporosis prevention. They would received a report with their average calcium intake based on their dietary records but would not be provided with recommendations for change.

### Proposed data analysis

All analyses will follow intention-to-treat principles when comparing intervention and control arms
[46]. Data from the second follow up will be analysed to compare short-term changes after the intervention. Data from the third follow up will be analysed to assess sustainability of any observed changes. The primary dependent variables are calcium intake (milligrams per day), moderate to vigorous intensity load-bearing physical activity level (duration in minutes per week).

### Cluster level analysis that adjusts for individual covariates and baseline measures

The main hypotheses will be tested using cluster-level analyses. This approach adheres to the recommendation of the 2004 Consort Statement for cluster randomised trials to fully account for the clustering effect
[46,47] and is recommended for studies with small number of clusters
[47,48]. Individual-level analysis using multi-level/mixed models was considered, but this study does not have the required cluster numbers for multilevel modelling as recommended by some analysts (minimum recommended is 15 cluster per arm)
[47].

This study will use the two-stage adjusted analysis based on cluster summaries developed by Hayes and Moulten (2009, pp182-184)
[47]. In stage one, SPSS linear regression will be run to generate an unstandardised residual for each subject (the difference between the observed value and the fitted value from the model for each individual participant). Baseline calcium value for each subject will be controlled for in the linear regression model. Other variables that were identified as potential confounders will also be included in the model as factors or covariates. This step incorporates repeated measures into the analysis and generates the covariate-adjusted residuals for each individual.

Cluster summaries for the covariate-adjusted residuals are then generated using SPSS descriptive statistics. These summaries are for stage two of the analysis, which is the cluster level analysis. The cluster means of the residuals are then compared in a cluster level analysis using a weighted *t*-test, with weighting based on cluster size (number of participants per cluster).

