### Importance of this study for osteoporosis prevention at population level

Existing evidence points to unrealised potential in both intervention design and settings when addressing osteoporosis prevention. This study improves on previous research as follows:

1. It is the first to address dietary and physical activity components each with unique intervention strategies in the context of osteoporosis prevention.

2. The intervention design for both behaviours is guided by Bandura's self-efficacy theory. The design focused on behavioural strategies rather than cognitive strategies to increase subjects' self-efficacy to change behaviour.

3. The utilisation of a workplace platform to address the risk associated with low levels of physical activity at work.

4. The use of an evidence-based approach when setting the intervention outcomes. Targeted behavioural outcomes were supported by evidence with the potential to affect the burden of osteoporosis.

5. This study compared a strengthened intervention design to a standard care control, which was current conservative practice. The results would indicate the degree to which the intervention design improves on current practice.

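### The stage-one residual difference is a valid test statistic, but as an effect size it is the adjusted arm difference times (1 − R² of arm on the covariates), so any effect reported in mg/day or min/week should be rescaled

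*Protocol article*

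**What the plan says.** The section on cluster-level analysis commits to a published method: "This study will use the two-stage adjusted analysis based on cluster summaries". Stage one works on individual women: "In stage one, SPSS linear regression will be run to generate an unstandardised residual for each subject", the residual being observed minus fitted. On the terms in that model it says "Baseline calcium value for each subject will be controlled for in the linear regression model" and "Other variables that were identified as potential confounders will also be included in the model as factors or covariates". Arm is not among the listed terms, though the text does not say outright that it is excluded. Stage two reads "The cluster means of the residuals are then compared in a cluster level analysis using a weighted" t-test, with weights equal to the number of women per workplace.

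No other comparison of the arms is described. The section on the importance of the study says "The results would indicate the degree to which the intervention design improves on current practice", and the sample size section sets targets of 250 mg/day and 60 minutes/week.

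**The concern.** A regression without arm credits to the covariates whatever part of the arm effect lines up with arm imbalance in those covariates. The residuals then carry only what is left. Entering arm in stage one would not help: ordinary residuals from that model have an arm difference of exactly zero. On neither reading is the difference in mean residuals the full covariate-adjusted difference.

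The amount lost depends on how closely the covariates are associated with arm, and this design leaves room for some association:

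- There are eight workplaces per arm, allocated from one ordered list without stratification ("The first eight workplaces in this new arrangement were assigned to the intervention group").
- The planning ICC for calcium is 0.5.
- Women are recruited after allocation, by coordinators who have already had an arm-specific briefing.
- The confounder list is open. Candidates collected at baseline include "indicators of socio-economic status (such as personal and household income, education level), religious preference", smoking, alcohol, family history, marital status and number of children, about nine in all.

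At stake is the size of the effect set against the 250 mg and 60 minute targets, not the p-value.

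**Working it through.** **Inputs from the protocol.** Sixteen workplaces of 20 (320 women). Calcium: SD 290 mg, ICC 0.5, effect 250 mg. Activity: SD 150 min, ICC 0.05, effect 60 min. α = 0.05, power 0.90.

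**Inputs assumed.** Correlation of baseline with follow-up 0.5; each outcome adjusted for its own baseline; five or nine added covariates, each with ICC 0.05 to 0.2. The documents give none of these figures.

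**Reproducing the plan's figures.** The plan gives no figure for the residual analysis, so I checked that I read its inputs correctly against Table 1.

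- Calcium: n = 2 × (290 × (1.960 + 1.282)/250)² = 28.3. The design effect is 1 + 19 × 0.5 = 10.5, and 28 × 10.5 = 294, or 14.7 workplaces, as stated.
- Activity: n = 131.3. The design effect is 1 + 19 × 0.05 = 1.95, and 131 × 1.95 = 255, or 12.8 workplaces, stated as 13.

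**Identity.** With size weights, the arm difference in workplace mean residuals is the individual-level arm difference in residuals. By the Frisch–Waugh–Lovell theorem:

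residual difference = b_adj × (1 − R²)

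Here b_adj is the arm coefficient with arm in the model, and R² comes from regressing arm on the stage-one covariates. The identity held in every simulated trial.

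**Expected R² by chance alone.** Each covariate contributes about (design effect)/(320 − 1).

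- Baseline calcium: 10.5/319 = 3.3%.
- Baseline activity: 1.95/319 = 0.6%.
- Nine covariates at ICC 0.05: 9 × 1.95/319 = 5.5% more.

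**Simulation (2,000 to 4,000 trials per scenario).** The table gives the residual difference as a share of b_adj.

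| Stage-one covariates | Calcium | Activity |
|---|---|---|
| Baseline only | 0.968 | 0.994 |
| + 5 at ICC 0.05 | 0.94 | 0.96 |
| + 5 at ICC 0.2 | 0.90 | 0.92 |
| + 9 at ICC 0.05 | 0.92 | 0.94 |
| + 9 at ICC 0.2 | 0.85 | 0.87 |

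With baseline only, 250 × 0.968 = 242 mg and 60 × 0.994 = 59.6 min. About one calcium trial in ten has a factor below 0.91.

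**Baseline imbalance.** The chance standard error of the arm difference in baseline calcium is 290 × √(4 × 10.5/320) = 105 mg. For a systematic imbalance averaging 200 mg, R²/(1 − R²) ≈ 0.25 × (200² + 105²)/290² = 0.152, so R² ≈ 0.13. The simulation gave 218.9 mg against 251.7 mg after rescaling, a factor of 0.87.

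**Validity.** Type I error of the weighted t-test stayed between 3.2% and 5.8% across the null scenarios. Read as an interval for the effect, the unscaled 95% interval covered about 92% in the worst row above (calcium, nine covariates at ICC 0.2).

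**Rescaling.** Dividing by (1 − R²) returned 247–253 mg and about 60 min, with 95–97% coverage and the same p-value. RMSE rose by about 5% in the least favourable cases.

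**The case against.** The strongest reply is that the section specifies a test, and the test is sound. It says the main hypotheses will be tested and ends with a t-test. It names neither an effect estimate nor a confidence interval, and an article may leave those to a fuller plan. It also cites a published procedure, and whether the cited pages include an estimation step cannot be checked here.

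Much of this stands. Three stronger readings are tempting, and the documents support none of them.

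- **That omitting arm is an error.** It is not. The residual test needs arm left out, and its type I error is close to nominal.
- **That the published effects will be materially shrunk.** The text does not name the residual difference as the effect to be reported. With the one covariate it does name, the calcium loss of 8 mg is under 0.1 of the 105 mg standard error. The larger losses rest on assumed covariate numbers and ICCs. The plan itself calls its ICC of 0.5 conservative, and a 200 mg imbalance would be about 1.9 standard errors under chance.
- **That every added covariate shrinks the estimate further.** Adding a covariate cannot lower R², but it also changes b_adj, so in a given trial the residual difference can rise. The shrinkage is relative to the same model's adjusted estimate, or on average.

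What remains is that the written steps yield only one quantity in mg/day or min/week, the residual difference, and the study promises to show a degree of improvement. That quantity follows from a stated rule, so the point concerns more than an omitted detail.

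**Conclusion.** The point holds as one of estimation, not of testing. The size-weighted residual difference is a valid test statistic but understates the adjusted arm difference by the factor (1 − R²). With baseline alone the loss is about 3% for calcium and 0.6% for activity, which is trivial. With five to nine clustered confounders it is roughly 6–15% for calcium and 4–13% for activity. An assumed 200 mg baseline imbalance gives about 13% for calcium. The identity is exact; the percentages depend on the assumed baseline correlation, covariate numbers, covariate ICCs and imbalance. The remedy is a cheap improvement to the reported effect size and does not repair an invalid test.

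**What to change.** State that arm is omitted from the stage-one regression, and keep the weighted t-test and its p-value. For any effect reported in mg/day or min/week, regress the arm indicator on the same covariates in the same women, take R², and divide the residual difference and both confidence limits by (1 − R²).

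A short covariate list fixed in advance would also keep R² small. Taking residuals with slopes from a model that includes arm removes the bias too, but in simulation with nine covariates it raised type I error to 7–9%, so I would not use it for the test.

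The cost is a sentence in the analysis section and one extra regression per outcome and visit, with no new data. The interval widens by the factor 1/(1 − R²), and RMSE is slightly larger.
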